#### Follow-Up: 1- and 2- Years Postpartum

Additional follow-up visits will occur at 1 and 2 years postpartum (1 month earlier or later) at the participants’ homes. The questionnaire includes maternal and child health and anthropometric measurements (as done at 1 month), breastfeeding and infant feeding, Caregiver Reported Early Development Instruments–long form [49], Me As A Parent Scale [50], Perceived Stress Scale, Brief Infant Sleep Questionnaire–short form [51], maternal intimacy and behavioral measurements (diet, tobacco use, and alcohol consumption), and other questions about daycare, screen time, baby-led weaning, and parenting styles. At 2 years postpartum, child development will also be assessed using the Global Scale for Early Development–long form [52]. Mother and infant hemoglobin levels, along with infant feces and human milk samples, will also be collected.

### Outcomes

The primary study outcome is the prevalence of EBF at 6 months postpartum as well as EBF duration. The secondary outcomes will include complementary breastfeeding duration and child development. Bile acids and other human milk components will be evaluated to determine the relationship with infant gut microbiota and infant growth and development.

### Statistical Analysis

All participants enrolled in this study will be included in the analysis and will be assessed by intervention group (control, unconditional, and conditional). EBF duration will be analyzed after completion of end line visits using an adjusted Cox proportional hazards model to estimate hazard ratios and 95% CI limits. We will use an adjusted logistic regression model to assess EBF at 6 months in the intervention and control groups. A complete case analysis will be used to address missing data.

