**Figure 1 figure1:**
[figure not shown]
Study timeline.

At baseline, mothers will be randomly assigned to one of the three groups (Figure 2): (1) control group—no intervention; (2) intervention arm 1—receipt of a social transfer at the 6-month visit; and (3) intervention arm 2—receipt of a social transfer at the 6-month visit, conditional on EBF status at the 6-month visit. All 3 groups will receive educational material on breastfeeding. The intervention is structured into 3 study arms to enable comparison between the 2 intervention groups and the control group, allowing us to evaluate the effects of conditional versus unconditional programs. Evidence from LPDR has shown that conditional social transfers significantly improved EBF rates [27]. Bolsa Família is another example of a successful conditional social transfer program for child health outcomes [34]. By contrast, our qualitative study found that participants expressed concerns about conditional programs targeting breastfeeding outcomes, particularly due to the pressure placed on mothers and the lack of reliable tools to accurately assess EBF. Given this context, we aim to evaluate both types of interventions to determine their respective impacts and assess which intervention is more effective and feasible for potential large-scale implementation.

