### Study Design

This study includes 5 visits: at birth (baseline), 1 month, 6 months (end line), 1 year, and 2 years (Figure 3). At baseline, the participants will complete a short questionnaire, and biological samples will be collected from both the mother and infant. At the end of the visit, the nurse will provide detailed information on the intervention depending on the group the mothers are randomly assigned to. If the mothers are assigned to an intervention group, they will be given a gift catalog to choose a social transfer for the visit at 6 months. The catalog will offer gift packages ranging from baby clothes, hygiene products, transportation vouchers, and developmental toys for the child. All 3 groups will receive educational pamphlets explaining the benefits of breastfeeding and providing breastfeeding guidelines.

During the follow-up visits (at 1 month, 6 months, 1 year, and 2 years), data collection will include a questionnaire and biological samples from both the mother and infant. The intervention groups (unconditional and conditional) will receive a social transfer at the 6-month visit. For mothers in the conditional group, assessors will review the maternal feeding reports as well as visually verify milk expression during biological collection.

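### Complete case is the only stated missing-data rule; it conflicts with including everyone enrolled and may bias the 6-month EBF comparison, because the gift is tied to the outcome visit

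*Protocol article*

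**What the plan says.** The Statistical Analysis section of the protocol article opens with the analysis population: "All participants enrolled in this study will be included in the analysis and will be assessed by intervention group (control, unconditional, and conditional"). It then names an adjusted Cox model for EBF duration and, for the 6-month outcome, "We will use an adjusted logistic regression model to assess EBF at 6 months in the intervention and control groups". It closes with "A complete case analysis will be used to address missing data". The article names no other missing-data method and no sensitivity analysis.

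Under Outcomes, "The primary study outcome is the prevalence of EBF at 6 months postpartum as well as EBF duration". The gift is tied to the visit that measures the first of these. Study Design states that "The intervention groups (unconditional and conditional) will receive a social transfer at the 6-month visit". The description of the arms under Recruitment (after Figure 1) defines the conditional arm as "receipt of a social transfer at the 6-month visit, conditional on EBF status at the 6-month visit". Control mothers receive no transfer. Mothers are told the terms of their group at baseline, and those in the intervention arms choose a gift then.

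**The concern.** There are two problems.

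**Consistency.** Both models are adjusted, so a complete-case rule removes from the 6-month analysis any mother without a 6-month outcome or with a missing covariate. Some missing data must be expected: Ethical Considerations allows withdrawal at any time, with deletion of data on request. The opening and closing sentences of the section then describe different sets of mothers.

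**Bias.** Complete case gives a fair comparison if loss is unrelated to EBF status given arm and covariates. Here the incentive to be seen at 6 months differs by arm. In the conditional arm it also differs by the outcome, because a mother who has stopped EBF knows that she no longer qualifies for the chosen gift. If such mothers are seen less often, the mothers left in the analysis show too much EBF. That would favour the arm that the article expects to do best. The rule also discards information already collected, since infant feeding is recorded at 1 month.

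**Working it through.** **Inputs.** Control EBF of 32.5% and planned arms of 200, 100 and 100 come from Sample Size and Power Calculation. The gift schedule comes from Recruitment and Study Design. The article gives no loss rate, overall or by arm, so every loss rate below is an assumption. A two-sided 5% test is also assumed, because the article states only 95% confidence limits. The plan has no figure of its own on this point to reproduce.

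**Formula.** Let p be the true EBF proportion in an arm, and L_E and L_N the proportions lost among EBF and non-EBF mothers. Complete case reads

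p(1 − L_E) / [p(1 − L_E) + (1 − p)(1 − L_N)].

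The odds in the arm are thus multiplied by (1 − L_E)/(1 − L_N), and the odds ratio by the conditional-arm factor divided by the control factor. If loss depends only on arm and EBF status, the same multiplier applies within every covariate stratum, so adjustment does not remove it. If loss depends on arm alone, each factor is 1 and there is no bias.

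**Scenarios with no true effect (p = 32.5% in both arms).** Example for the first row: 0.325/(0.325 + 0.675 × 0.9) = 0.325/0.9325 = 34.9%.

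| Conditional loss, EBF / non-EBF | Control loss, EBF / non-EBF | Conditional reads | Control reads | Difference (points) | Odds ratio (true 1.00) |
|---|---|---|---|---|---|
| 0 / 10% | 10 / 10% | 34.9% | 32.5% | +2.4 | 1.11 |
| 0 / 20% | 10 / 10% | 37.6% | 32.5% | +5.1 | 1.25 |
| 0 / 30% | 10 / 10% | 40.8% | 32.5% | +8.3 | 1.43 |
| 5 / 25% | 10 / 10% | 37.9% | 32.5% | +5.4 | 1.27 |
| 0 / 20% | 0 / 20% | 37.6% | 37.6% | 0.0 | 1.00 |
| 0 / 10% | 0 / 20% | 34.9% | 37.6% | −2.7 | 0.89 |
| 0 / 10% | 0 / 30% | 34.9% | 40.8% | −5.9 | 0.78 |
| 5 / 15% | 5 / 35% | 35.0% | 41.3% | −6.3 | 0.76 |

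For the first three rows, with 180 controls and 100 × (0.325 + 0.675(1 − L_N)) conditional mothers analysed, the chance of a significant result is about 7%, 13% and 25% instead of 5%.

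**With a true effect (47% against 32.5%, odds ratio 1.84).** Conditional loss of 5% among EBF and 25% among non-EBF mothers, with 10% random loss in control, reads 52.9% against 32.5%, an odds ratio of 2.33.

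**Check on the obvious alternative.** Take the first row and count every missing mother as not EBF. Control becomes 0.325 × 0.9 = 29.25% and the conditional arm stays at 32.5%. That is a spurious +3.25 points, larger than the +2.4 from complete case. This rule is therefore not a safe primary analysis either.

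**The case against.** The strongest objection is to the stronger reading, that complete case will overstate EBF in the conditional arm. A reader might infer this from the gift schedule, but the documents do not support it. Nothing in them says that the gift changes who is seen. The End line section makes the 6-month visit an at-home one, so the nurse goes to the mother. Ethical Considerations promises a small gift to mothers who stop breastfeeding involuntarily, without saying in which arm. Controls have no gift at all, so their loss may be just as selective or more so. These points stand, and they limit the finding to a risk of unknown direction. They do not remove it: a home visit can be declined, and the small gift does not cover a mother who stops by choice.

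The opening sentence can also be read as analysis by allocated group among mothers with data. That is a fair reading of what was probably meant, but the text does not say it.

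A reader might further infer that the Cox model would delete mothers lost after 1 month. The section does not say so, and censoring is inherent in that model. What stands is that a general complete-case sentence leaves the question open.

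Finally, an analysis plan that is not shown may add sensitivity analyses. The point here concerns the rule that the article does state.

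**Conclusion.** The point holds as a risk, not as a demonstrated bias. As written, the section includes everyone and also drops incomplete cases. The gift schedule gives a concrete reason why loss may depend on arm and, in the conditional arm, on EBF. Complete case may then bias the primary comparison, possibly in favour of the conditional arm.

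Under the assumed loss rates with no true effect, the difference runs from −6.3 to +8.3 points and the odds ratio from 0.76 to 1.43. The 34.9% to 40.8% range belongs to one favourable pattern: random loss in control and no loss among EBF mothers in the conditional arm. None of these figures is a forecast. Because the direction cannot be known in advance, the handling of missing data should be fixed before results by arm are seen.

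**What to change.** Replace the complete-case sentence with the following.

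- **One analysis set:** all randomised mothers, as allocated, apart from any whose data are deleted at their request; report that number by arm.
- **Use of 1-month data:** a mother already known to have stopped EBF is not dropped when the 6-month visit is missed. If EBF at 6 months means uninterrupted EBF since birth, her outcome is known to be not EBF. If it means feeding status around the visit, her 1-month status enters the imputation. The text should say which definition applies.
- **Primary handling of the rest:** multiple imputation of 6-month EBF within arm, from baseline and 1-month data.
- **Cox model:** cessation already recorded counts as an event; mothers lost to follow-up while still EBF are censored at the last visit with known EBF status.
- **Reporting:** 6-month loss by arm.
- **Sensitivity:** imputation assumes missing at random and so does not remove loss that depends on 6-month EBF itself. Ordinary censoring has the same limit. Pre-specify an arm-specific delta or tipping-point analysis, with missing counted as not EBF and complete case as further sensitivity analyses.

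The cost is wording and a little programming, with no new data. The article expects the primary outcome to be complete by May 2026; the change should be dated before any comparison by arm.

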### Data Management

ODK software will be used to collect and manage the study data. Questionnaires are uploaded onto the ODK platform before data collection, allowing study staff to access the questionnaire offline using a tablet or smartphone. All data collection devices are password protected and stored securely at the hospital when they are not in use. Once the questionnaires are filled out, they are uploaded onto the server and are accessible through a secure web interface, ODK Aggregate. Only authorized personnel who require the data to fulfill their duties within the scope of the research project will be able to access ODK Aggregate.

The collected data will be stored on the secure ODK server and will only be identifiable by a unique participant number. The biological specimen samples will only be identifiable by the same unique participant number. The biological specimens will be stored securely at the University of São Paulo and will only be accessible to authorized personnel. Health-related data will be stored for 15 years, following the University of São Paulo regulations. If participants sign a separate consent form for reusing health data, data and biological samples will be kept for an unspecified amount of time.

### Ethical Considerations

This study was submitted and approved by the National Commission for Ethics in Research and the University Hospital of the University of São Paulo in Brazil (6.704.768), and it was submitted for ethical review to the Ethical Commission of Northwestern and Central Switzerland (AO_2024-00015). The study will be carried out in accordance with the Declaration of Helsinki. Any amendments to the protocol, ICF, or any other forms related to the study have to be reviewed by an independent ethics committee.

Eligible participants will be identified by study staff, and an initial visit will occur at the hospital. The nature of the study will be explained to the participants orally before obtaining a written ICF. Once the participants have some time for reflection and to answer any questions, they will be asked to sign an ICF according to their assigned group. For minors (aged <18 years), both the mother and her parents will be required to provide consent. For participants who are illiterate, an additional witness will be required. Participation is voluntary, and participants have the right to withdraw from the study at any given point in time with no further obligations. If the participant decides to withdraw from the study at any time, they may request that their data will be deleted and their biological specimen samples destroyed.

Project data and biological materials will be handled with the utmost discretion and will be accessible only to authorized personnel who require the information to perform their duties within the scope of the research project. Participants will be identified solely by a unique participant number and participants will be assured that all personal information collected during the research study will be kept confidential. Given that the intervention is primarily designed to support mothers, adverse outcomes seem unlikely. Breast milk samples will be collected through hand expression, which should not be painful for participants. For the hemoglobin measurements, blood will be collected through a finger prick, which can lead to a small discomfort for the participants. The risk of inflammation or infection is small if the participants follow proper hygienic procedures. If the participant feels any discomfort, the process will be stopped. Breastfeeding mothers may experience mastitis, which may affect breastfeeding. We will provide information and advice in the educational pamphlets on how to treat the infection without having to stop breastfeeding, as recommended by the WHO.

A social transfer will be provided to participants in the intervention groups. Four gift package options will be given to allow individualized social transfers. If any negative themes arise (eg, stigma), strategies to overcome these will be identified during the qualitative study. In the case that mothers involuntarily stop breastfeeding, a small gift will be provided.

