**Figure 2 figure2:**
[figure not shown]
Study arms.

The study participants will be contacted at the hospital after giving birth. New mothers will be eligible to participate in the study if they (1) gave birth in the last 72 hours, (2) are exclusively breastfeeding at the time of recruitment and intend to continue to exclusively breastfeed, (3) are beneficiaries of the Bolsa Família program or part of the eligible population for Bolsa Família registered in the Unified Social Assistance Registry (Cadastro Único), (4) live in São Paulo, (5) have no illnesses that contraindicates breastfeeding, (6) had a healthy singleton infant of 37 weeks or more gestation with a birth weight of at least 2500 g, and (7) agree to participate and sign an informed consent form (ICF). If underage (aged between 12 and 17 years), a legal representative will also have to agree to sign the informed consent.

A team of 2 nurses will be responsible for enrollment and follow-up of participants. The nurses will explain the study to all participants and collect the written ICF. Randomization will be done using a simple random number draw generated by ODK, used to collect data on tablets. The nurses will not have access to the random allocation sequence.

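### One clause has mothers sign a consent form chosen by assigned group, while other sections suggest consent before the draw; if the clause is followed, refusals can differ by arm

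*Protocol article*

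**What the plan says.** Four sections of the protocol article bear on the order of consent and allocation.

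- **Ethical Considerations.** The sequence is an oral explanation, time to reflect, then signature: "The nature of the study will be explained to the participants orally before obtaining a written ICF", after which "they will be asked to sign an ICF according to their assigned group".
- **Recruitment (text after Figure 2).** Signing the consent form is the seventh eligibility criterion. The section then says "The nurses will explain the study to all participants and collect the written ICF", and in the next sentence "Randomization will be done using a simple random number draw generated by ODK, used to collect data on tablets". It adds: "The nurses will not have access to the random allocation sequence".
- **Study Design.** The baseline questionnaire and biological samples are described first. Then: "At the end of the visit, the nurse will provide detailed information on the intervention depending on the group the mothers are randomly assigned to".
- **Statistical Analysis.** "All participants enrolled in this study will be included in the analysis", by intervention group, with complete case analysis for missing data.

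The Recruitment section (text after Figure 1) also reports that participants in the preparatory qualitative study were worried about conditional programs, partly because of the pressure on mothers.

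**The concern.** A form selected by assigned group can be signed only once there is a group. If that is the practice, the nurse knows the arm at the moment of consent, and the mother may learn it from the form. She can then decline because of it. Since signature is an entry criterion, a mother who declines is not enrolled and drops out of the comparison without appearing as a loss.

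This matters if refusal is linked to both the arm and the outcome. A mother who doubts that she can sustain EBF for 6 months has a reason to decline an arm whose transfer depends on it. The conditional arm would then hold mothers more likely to succeed anyway, and randomisation would no longer protect that comparison. Covariate adjustment cannot be relied on to repair this, because confidence and firmness of intention may not be captured by the covariates.

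**Working it through.** **Step 1: the order of events, section by section.** No figure in the plan is at stake, so the first check is textual.

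| Section | What it implies | Is the order stated? |
|---|---|---|
| Ethical Considerations | Assignment, then signature | Yes, by the wording of the clause |
| Recruitment | Signature, then draw | No; inferred from sentence order and from signature being an entry criterion |
| Study Design | Arm details come last at baseline, so consent for the questionnaire and samples should already have been given | No; inferred |
| Statistical Analysis | Enrolled mothers are analysed | Enrolled is not defined against randomised |

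The Ethical Considerations clause does not fit easily with the two operational sections. None of them says outright that consent precedes the draw.

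**Step 2: how large a bias could be.** Inputs:
- Control EBF of 32.5% and a planned rate of 47% in either intervention arm (Sample Size and Power Calculation), so a planned effect of 47 − 32.5 = 14.5 points.
- Assumption: no true effect, so EBF is 32.5% in every arm.
- Assumption: a fraction *f* of mothers who would not sustain EBF declines after learning the arm, in the conditional arm only. No mother who would sustain EBF declines.

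Observed EBF in the conditional arm = 0.325 / [0.325 + 0.675 × (1 − *f*)].

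| *f* | Share of arm refusing (0.675 × *f*) | Observed EBF | Spurious difference |
|---|---|---|---|
| 10% | 6.75% | 0.325/0.9325 = 34.9% | +2.4 points |
| 20% | 13.5% | 0.325/0.865 = 37.6% | +5.1 points |
| 30% | 20.25% | 0.325/0.7975 = 40.8% | +8.3 points |

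**Step 3: relaxing the assumption about who refuses.** Let *r* be the share of the conditional arm that refuses and *q* the EBF rate those mothers would have had. Observed EBF = (0.325 − *r* × *q*) / (1 − *r*). The last column is the chance that a two-sided 5% pooled two-proportion test with 200 v 100 enrolled rejects when there is no true effect.

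| *r* | *q* | Observed EBF | Spurious difference | Rejection rate |
|---|---|---|---|---|
| 5% | 10% | 33.7% | +1.2 points | 5.6% |
| 10% | 10% | 35.0% | +2.5 points | 7.3% |
| 20% | 10% | 38.1% | +5.6 points | 16.5% |
| 30% | 10% | 42.1% | +9.6 points | 37.7% |
| any of these | 32.5% | 32.5% | 0 | 5.0% |

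**Step 4: when the bias vanishes.** The last row shows no bias when refusers have the same EBF rate as everyone else. If the same fraction of non-sustaining mothers declined in the control arm too, both observed rates would rise equally and the difference would again be zero. Bias needs refusal that differs by arm and is related to EBF.

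**The case against.** The case against is substantial.

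- **The order is not established.** A reader might infer that allocation is definitely known before consent. That rests on one clause in an ethics section, which may be loose wording, and the two operational sections point the other way. The article condenses a full protocol, and the consent forms are not shown, so whether they differ by arm cannot be checked. This stands. What the text supports is an inconsistency with a serious consequence under one reading.
- **Concealment.** A reader might infer that the concealment statement is false. It is not: the plan claims only that nurses cannot access the sequence, which holds under either order. But that statement does not address an arm already known when consent is sought.
- **The analysis set.** The plan says that enrolled mothers are included. It does not say that only they are. Still, with signature as an entry criterion, a mother who refuses has no evident route into the analysis.
- **The size is one-sided.** Step 2 assumes that only non-sustaining mothers refuse, and only in the conditional arm. Controls, who receive no transfer, may decline as well. Visits and samples are the same in all arms, a conditional mother may still gain a transfer, and a small gift is planned if breastfeeding stops involuntarily. Eligibility already requires current EBF and an intention to continue. All this stands, so the figures are illustrations. The reported worries about conditional programs make unequal refusal plausible, but they are not a refusal rate.
- **Relabelling the analysis set is no cure.** Mothers drawn but never consented have no outcome data, and complete case analysis would drop them again. This also stands and shapes the fix.

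**Conclusion.** The point holds as a contradiction that needs resolving, with a conditional threat to the primary comparison. Taken literally, the Ethical Considerations clause puts assignment before signature, while Recruitment and Study Design suggest the reverse. If the clause describes practice, the arm may be known at consent, refusal can differ by arm and be related to EBF, and refusers never enter the enrolled set.

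The documents do not show that such refusal has occurred and give no basis for estimating it. The range of 2.4 to 8.3 points is a worst case as to who refuses and in which arm, and its refusal fractions are assumed. If the clause is only loose wording, there is no bias from this source and the text alone needs correcting.

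**What to change.** 1. **Make the three sections agree.** State in Recruitment, Study Design and Ethical Considerations that one common consent form describing all three arms is signed before the draw. In ODK, hold back the draw until the eligibility and consent fields are complete. Apply this to all remaining recruitment. With 204 of 400 enrolled as of September 2025, 400 − 204 = 196 dyads were still to come at that date.
2. **Audit the mothers already approached.** Match every draw that ODK retained against a signed consent, and report by arm the number drawn, the number consenting and the number refusing after the draw. If draws without consent were not retained, say so.
3. **If there were post-draw refusals, add a sensitivity analysis.** For each arm, compute EBF among all drawn as (1 − *r*) × observed EBF + *r* × *q*, with *r* taken from the audit and *q* varied over a stated range. For example, *r* = 10%, observed EBF 35.0% and *q* = 10% give 0.9 × 0.35 + 0.1 × 0.10 = 32.5%, the true rate assumed in Step 3. Redefining the analysis set as all randomised does not replace this, because the refusers' outcomes were never collected.

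The cost is a consent form amendment to the ethics committees, a small ODK form change and the time for the audit. No additional participants are needed.
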